| Plan for addressing confounding Age and sex will be adjusted for in all analyses as potential confounders of associations between ethnicity and prescribing. The potential mediating influences of smoking, BMI, polypharmacy, multimorbidity, patient adherence, patient engagement, diabetes duration and HbA1c will be quantified by adjusting regression models for each of these variables in turn. |
| Plans for addressing missing data Monitoring and treatment of type 2 diabetes is incentivised by the UK’s primary care Quality Outcomes Framework (QOF), therefore recording of cardiovascular risk factors and some other of the covariates mentioned above is likely to be more complete than for other disease areas. Where these factors are missing, we will use complete case analysis as data may not be missing at random.  Missing ethnicity data is the chief concern. Given that ethnicity data are unlikely to be missing at random, multiple imputation methods are not appropriate, and we will perform complete case analysis instead. Complete case analysis will be unbiased if missingness is independent of the outcome, conditional on model covariates. One of the main reasons that missingness would be expected to be associated with prescribing patterns is that people who are poorly engaged with their GP may be less likely to have ethnicity recorded (whatever their ethnicity), or be eligible to be prescribed medication. However, as discussed above we plan to adjust for number of consultations in the year prior to diagnosis. Within those with similar levels of GP contact prior to diabetes diagnosis, it is less conceivable that missingness of ethnicity will be strongly associated with prescribing patterns. Additionally, three sensitivity analyses (see section N) will be performed to boost ethnicity recording. |
| Patient or user group involvement (if applicable) A study steering group will be convened consisting of the collaborators and several people with type 2 diabetes, ideally representing each ethnic group. These individuals will be recruited from the pool of participants from the SABRE study (Southall and Brent Revisited, PI: NC) and will meet annually to discuss the study progress, results and dissemination of findings. Key results will be reported via the media, Diabetes UK website, Living with Diabetes events and “Balance” magazine (for Diabetes UK members), to make people with diabetes aware of the findings. |

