| Objectives, Specific Aims and Rationale Overall aim  To investigate ethnic differences in prescribing for type 2 diabetes in UK primary care.  Objectives  For people of European, South Asian and African Caribbean origin, ethnic differences in the following will be investigated:   1. Proportions of people with: a) incident hypertension started on antihypertensives and b) an elevated 10 year CVD risk score (according to QRISK, ASSIGN, JBS2, Framingham or unspecified risk-estimating equations (26)) being commenced on statin treatment. 2. Time to initiation of first-line anti-diabetic/ antihypertensive/lipid-lowering medication 3. Choice of anti-diabetic (first- to third-line), antihypertensive and lipid-lowering medication 4. Doses used for each anti-diabetic, antihypertensive and lipid-lowering medication 5. Monitoring rate after medication commencement 6. Time to medication intensification (up-titration, addition or switching) after detection of sub-optimal control of diabetes, hypertension or blood lipids   Additionally, we will examine potential confounding or mediating role/s of:   1. Smoking, BMI, deprivation, polypharmacy, multi-morbidity, drug adherence (for objectives v) and vi)), patient engagement with healthcare, diabetes duration and HbA1c (in people with diabetes).   Null hypotheses   1. No ethnic difference in proportions of people started on a) antihypertensives or b) statin treatment will be detected. 2. No ethnic difference in time to initiation of first-line anti-diabetic, antihypertensive or lipid-lowering medication will be detected. 3. Regarding choice of medication: 4. No ethnic difference in the proportions of people prescribed metformin as first-line, or sulphonylureas, DPP4-inhibitors, thiazolidinediones, SGLT2 inhibitors, GLP1 agonists or insulin as second- or third-line diabetes treatment will be observed. 5. No ethnic difference in the proportions of people prescribed ACE inhibitors/ angiotensin-receptor blockers, calcium-channel blockers or thiazide diuretics for hypertension will be observed. 6. No ethnic difference in the proportions of people with ≥10% cardiovascular disease risk who are prescribed lipid-lowering medication will be observed. 7. No ethnic difference in the proportions prescribed the maximum dose of anti-diabetic, antihypertensive or lipid-lowering medication will be observed, and the modal dose for each class will not differ by ethnicity. 8. No ethnic difference in the monitoring rates of anti-diabetic, antihypertensive or lipid-lowering medication will be observed. 9. No ethnic difference in time to treatment intensification (after the detection of sub-optimal control) of anti-diabetic, antihypertensive or lipid-lowering medication will be observed. 10. Associations between ethnicity and prescribing will not be confounded or mediated by smoking, BMI, deprivation, polypharmacy, multi-morbidity, drug adherence, patient engagement, diabetes duration or HbA1c (in people with diabetes).   Rationale  Research indicates that control of diabetes and its allied cardiovascular risk factors is poorer in UK’s minority ethnic groups than in the background white population. Crucially, these discrepancies are likely to contribute to higher rates of heart disease and stroke, in people with and without diabetes, seen in these groups. By examining the associations above, this study seeks to determine whether ethnic differences in prescribing for people with and without diabetes are present, and explanations for them.  It is important to compare prescribing in people with and without diabetes for each ethnic group. Our previous work suggests that diabetes is a much more potent CVD risk factor in people of South Asian and African Caribbean-origin than those of European-origin, and differential prescribing of statins and anti-hypertensives in those with vs. without diabetes is a possible explanation for this.  If ethnic inequalities in prescribing are present, their identification may influence future prescribing recommendations and thus eventually lessen the personal and societal burden of diabetes and cardiovascular disease complications in ethnic minority groups. |

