| O. Data/ Statistical Analysis For all parts of the study, the population will be people with and without new-onset type 2 diabetes active in CPRD from 2006 (see section K, above) and the exposure will be ethnicity (either South Asian vs. European [baseline] or African Caribbean vs. European [baseline], as detailed in section L, above). Covariates in base models will include age and sex, and further covariates will be considered individually, as outlined in section vi) below. Statistical analysis is further considered by objective:   1. **Outcome:** Proportion of those eligible for primary prevention who are prescribed a) antihypertensives and b) lipid-lowering medication   **Entry:** Date of incident a) hypertension Read code/ raised BP reading or b) elevated 10 year CVD risk score, at least 12 months after study start date of 1^st^ January 2005  **Exit:** First of; date of first antihypertensive/ lipid-lowering medication prescription (defined by the absence of a prescription for the medication in the previous 6 months’ records), end of study, leaving CPRD practice or death  **Analysis:** Proportions receiving antihypertensives/ statin will be compared by ethnicity, then logistic regression models will be used to adjust for confounding/ investigate potential mediators  **Example effect measure:** Odds ratio (OR) of receiving an antihypertensive/ lipid-lowering medication vs. not for each ethnic group of interest, stratified by time period since identification of hypertension/ elevated CVD risk   1. **Outcome**: time to initiation of first-line anti-diabetic/ antihypertensive/ statin, probability of receiving anti-diabetic/ antihypertensive/ statin at one year post-diagnosis/ identification of high CVD risk   **Entry**: date of type 2 diabetes diagnosis/ incident hypertension Read code or raised BP reading/ incident high 10 year CVD risk score recording  **Exit**: date of first anti-diabetic/ antihypertensive/ statin prescription (defined by the absence of a prescription for the medication in the previous 6 months’ records), or end of study/ leaving CPRD practice/ death  **Analysis**: summary statistics will be compared by ethnicity using Kaplan-Meier time-to-event analysis (cumulative failure probability in a given time frame by ethnicity, comparison of medians by log-rank test), Cox proportional hazards regression models will be used to adjust for confounding/ investigate potential mediators  **Example effect measure**: hazards ratio (HR) for anti-diabetic/ antihypertensive/ statin prescription   1. **Outcome:** proportions of patients prescribed medication from each anti-diabetic (stratified by first- to third-line treatment), antihypertensive and lipid-lowering class (defined by the absence of a prescription for the medication in the previous 6 months’ records)   **Sub-population:** a) all participants starting first- to third-line anti-diabetic treatment, b) all patients on antihypertensives, or c) all patients on lipid-lowering medication  **Analysis:** proportions receiving each drug will be compared by ethnicity, then logistic regression models will be used to adjust for confounding/ investigate potential mediators  **Example effect measures**: odds ratio (OR) of being prescribed metformin (=1) vs. non-metformin medication (=0) at first stage of treatment, OR of being prescribed sulphonylurea (=1) vs. non- sulphonylurea medication (=0) at second stage of treatment, OR of calcium-channel blocking antihypertensive prescription vs. non- calcium-channel blocking antihypertensive in those on antihypertensive treatment, OR of statin prescription vs. non-statin lipid-lowering medication prescription in those with >10% 10 year cardiovascular risk   1. **Outcome:** proportions of patients prescribed each dose of each anti-diabetic, antihypertensive and lipid-lowering medication, stratified by treatment stage (defined by the absence of a prescription for the medication in the previous 6 months’ records)   **Sub-population:** a) all participants on first- to third-line anti-diabetic treatment, b) all patients on antihypertensives, or c) all patients on lipid-lowering medication  **Analysis: :** proportions receiving each dose of each drug will be compared by ethnicity, then logistic regression models will be used to adjust for confounding/ investigate potential mediators  **Example effect measures**: OR of being prescribed maximum dose (2g daily) vs. sub-maximum dose of metformin, OR of being prescribed atorvastatin 10mg per day vs. higher doses (20mg, 40mg or 80mg)   1. **Outcome:** yearly monitoring rate post commencement of medication from each anti-diabetic (first- to third-line), antihypertensive and lipid-lowering class – i.e. number of times HbA1c/ blood pressure/ blood lipids measured per person-year of follow-up, stratified by year after commencement; may be multiple entry dates per person for different medications   **Entry:** first use of any medications of interest from 2006 onwards  **Exit:** first of; end of strata (e.g. 1 year after medication commencement), end of study/ leaving CPRD practice/ death  **Analysis:** summary statistics will be compared by ethnicity, Poisson regression modelling used to adjust for confounding/ investigate potential mediators  **Example effect measures**: yearly monitoring rate ratios (RRs)   1. **Outcome:** time to medication intensification (up-titration, addition or switching) after detection of sub-optimal control of diabetes, hypertension or blood lipids, or probability of intensification 1 year post-detection of sub-optimal control; may be multiple entry dates per person for different medications   **Entry:** date when sub-optimal risk factor control detected (see section M for how this is defined for each risk factor)  **Exit:** first of; date of anti-diabetic, antihypertensive or lipid-lowering treatment intensification, end of study/ leaving CPRD practice/ death  **Analysis:** summary statistics will be compared by ethnicity using Kaplan-Meier time-to-event analysis (cumulative failure probability in a given time frame by ethnicity, comparison by log-rank test), Cox proportional hazards regression models will be used to adjust for confounding/ investigate potential mediators  **Example effect measures**: cumulative failure probability for each ethnic group 1 year post detection of sub-optimal value, comparison of median survival times using the log-rank test by ethnicity, HRs of intensification stratified by year   1. **Outcome:** influence of deprivation, polypharmacy, multi-morbidity, drug adherence (iv) and v) only), patient engagement with healthcare, diabetes duration and HbA1c on any ethnic differences found in i) to v).   **Entry:** as above for i), iv) and v)  **Exit:** as above for i), iv) and v)  **Analysis:** as above for i) to v)  **Covariates:** smoking status, BMI, deprivation, polypharmacy, multi-morbidity, drug adherence, patient engagement with healthcare, diabetes duration and HbA1c  **Effect measures:** we will observe the degree of attenuation of the ethnic difference effect measure for each outcome when each covariate is inserted in turn to models, and thus evaluate the likelihood of confounding or mediation  Sub-group/ sensitivity analyses  See section O of original application  Plans for addressing misclassification and bias  See section O of original application  Multiple comparisons  See section O of original application |

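### Reading mediation from attenuation of the ethnic OR or HR understates the share explained, because these measures move away from 1 when any predictor of prescribing is added

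*Supplement*

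**What the plan says.** In the amendment of 9 December 2019, section O (Data/ Statistical Analysis) sets a base model and a sequence: "Covariates in base models will include age and sex, and further covariates will be considered individually". The last numbered item of that section gives the rule for explanation: "we will observe the degree of attenuation of the ethnic difference effect measure for each outcome when each covariate is inserted in turn" to models, "thus evaluate the likelihood of confounding or mediation". The section Plan for addressing confounding in the original application, which the amendment does not replace, says that the mediating influences "will be quantified by adjusting regression models for each of these variables in turn".

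The effect measure depends on the outcome:
- Proportion treated, drug choice and dose: "logistic regression models will be used to adjust for confounding/ investigate potential mediators", giving odds ratios.
- Time to initiation and time to intensification: "Cox proportional hazards regression models will be used to adjust for confounding/ investigate potential mediators", giving hazard ratios.
- Monitoring: "Poisson regression modelling used to adjust for confounding/ investigate potential mediators", giving rate ratios.

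The matching null hypothesis in the amended Objectives section begins: "Associations between ethnicity and prescribing will not be confounded or mediated by smoking, BMI". The plan gives no attenuation threshold, no covariate-standardised contrast and no formal mediation method, and it does not mention non-collapsibility. Crude proportions and Kaplan-Meier probabilities are planned, but only as unadjusted summaries.

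**The concern.** The rule treats the change in the ethnic effect measure as the part that the covariate explains. For ORs and HRs the change has two components. One is real: it arises when the covariate is distributed differently across ethnic groups and affects prescribing. The other is an artefact: it arises whenever the covariate predicts prescribing, even with identical distributions in every group, and it pushes the adjusted measure further from 1. The two oppose each other when the covariate truly explains part of the gap. The null hypothesis on confounding and mediation is therefore not what zero attenuation measures.

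The rare-outcome approximation does not help. By the plan's own figures the outcomes are common. Finding explanations for ethnic differences is part of the amended rationale, and the findings are meant to inform prescribing recommendations. Reporting that a covariate explains little, when it explains a moderate share, would weaken that use.

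**Working it through.** The documents state no figure for attenuation, so there is none to reproduce. The check asks how large the artefact is at the plan's outcome frequencies.

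**Inputs from the amended Sample size considerations.** Intensification at 1 year 24%; statins in high-risk people 24%; anti-diabetic at 1 year 42%; metformin first-line 73%; sulphonylurea second-line 87%; eligible hypertension untreated 21%, so 100% - 21% = 79% treated. Group sizes of 10.5K and 120.4K give a minority share of 10.5/130.9 = 8%.

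**Assumed, not in the documents.** One covariate Z, standard normal in Europeans; covariate OR of 1.5 to 5 per SD; covariate HR of 1.5 to 2.7 per SD; conditional ethnic OR or HR of 0.70.

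**Step 1: OR, covariate unrelated to ethnicity.** Model: logit P = a + ln(0.70) × minority + b × Z, with b the log covariate OR and a set so that Europeans have the stated frequency. Averaging over Z gives the OR without the covariate.

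Worked case, 42% outcome and covariate OR 2.7: a = -0.389, b = 0.993. The minority proportion is 34.98%. The base OR is (0.3498/0.6502)/(0.42/0.58) = 0.743, against 0.70 after adjustment. In logs, 0.357/0.297 = 1.20, so the log-OR grows by 20% with no confounding or mediation. The risk difference is -7.0 percentage points with or without the covariate.

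Growth of the log-OR on adjustment:

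| Outcome | Covariate OR 1.5 | 2 | 2.7 | 5 |
| --- | --- | --- | --- | --- |
| 24% | 2.7% | 7.9% | 15.8% | 37.9% |
| 42% | 3.7% | 10.4% | 20.0% | 45.2% |
| 73% | 3.4% | 9.5% | 18.4% | 42.1% |
| 87% | 2.1% | 6.3% | 12.9% | 32.0% |

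The relative growth hardly depends on the size of the ethnic gap: at a conditional OR of 0.90, with 42% and covariate OR 2.7, it is still 20% (base OR 0.916).

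**Step 2: HR, covariate unrelated to ethnicity.** Exponential conditional hazards, administrative censoring, 8% minority share, limiting value of the Cox estimate. Base HR for a conditional HR of 0.70, with growth of the log-HR:

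| Cumulative incidence | Covariate HR 1.5 | 2 | 2.7 |
| --- | --- | --- | --- |
| 24% | 0.705 (2%) | 0.715 (6%) | 0.731 (14%) |
| 42% | 0.709 (4%) | 0.726 (11%) | 0.749 (23%) |
| 79% | 0.720 (9%) | 0.749 (24%) | 0.780 (44%) |

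**Step 3: how much mediation can be missed.** Lower the covariate mean in the minority group until the base OR equals the adjusted OR. At 42% and covariate OR 2.7 this takes a shift of 0.071 SD. The minority proportion is then 33.64%, and the base OR is (0.3364/0.6636)/(0.42/0.58) = 0.70. Attenuation is zero. Yet the risk difference is -8.36 points, of which 34.98 - 33.64 = 1.34 points run through the covariate: 1.34/8.36 = 16%. Over outcomes of 24-87% and covariate ORs of 1.5-5, the share missed in this way is 2% to 31%.

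**Step 4: larger mediation.** At 42%:

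| Covariate OR | Shift (SD) | Log-OR attenuation | Share of risk difference |
| --- | --- | --- | --- |
| 2.7 | 0.2 | 23% | 34% |
| 2.7 | 0.3 | 35% | 44% |
| 2.7 | 0.5 | 50% | 56% |
| 1.5 | 0.3 | 23% | 24% |

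Larger shares are understated but remain visible, and with a weak covariate the two scales nearly agree.

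**The case against.** The strongest case for the plan is that the rule is descriptive. It sets no threshold, and the multiple-comparisons paragraph asks readers to weigh effect sizes rather than p values. A reader might infer that the plan tests for no change and would reject falsely at these sample sizes. It states no such test, so that inference fails. What stands is that the plan says mediation will be quantified this way, and the quantity is biased.

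The size rests on assumed covariate strength. For weak predictors it is negligible (2-4% of the log-OR at 1.5 per SD), and the documents do not say which of the listed covariates are strong. The zero-attenuation case is an exact cancellation; away from that point some attenuation shows. Both limits are accepted.

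A reader might infer that HbA1c is the obvious hidden mediator. The documents do not support this. The Study Background reports poorer glucose control in the minority groups. If that holds at baseline and a higher HbA1c prompts prescribing, then for an ethnic OR below 1 HbA1c would suppress the deficit rather than mediate it. Both movements would be away from 1 and nothing would cancel. Its direction is uncertain, so it should not serve as the example.

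Nor does the artefact create false mediation by itself: with a covariate unrelated to ethnicity the shift is away from 1, and the plan looks for movement towards 1.

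**Conclusion.** The point holds in a limited form. For the logistic and Cox outcomes, attenuation understates the share of an ethnic difference that a covariate explains, and it can miss small shares. The loss runs from trivial for weak covariates to substantial for strong ones, over the ranges in steps 1 to 3. Those ranges assume a conditional OR or HR of 0.70 and a single normal covariate. They need a non-null ethnic effect: with no ethnic difference and no imbalance in the covariate there is no shift. The Poisson monitoring rate ratios are collapsible and unaffected. A reader might also infer that the ethnic comparisons themselves are wrong. They are not: the fault lies only in comparing ORs or HRs between models to judge explanation. This is a cheap improvement to an explanatory objective.

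**What to change.** In section O, last numbered item, state that for logistic and Cox outcomes the change will be judged on a collapsible scale. Report the age-sex standardised ethnic difference in proportion (logistic) or in 1-year cumulative probability (Cox; a quantity the plan already names for initiation and intensification). Give it before and after standardising each covariate to the European distribution, in the same patients, with a bootstrap confidence interval for the change. For the logistic models the Karlson-Holm-Breen rescaled comparison is an alternative. Keep the ORs and HRs as effect measures, and keep the rate-ratio comparison for monitoring. Align the wording in Plan for addressing confounding.

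The cost is some extra computing and one more reported quantity per outcome and covariate; no new data are required. The change removes the scale artefact only. It does not by itself tell confounding from mediation.
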